## Methods/Design

### Research design

This study is a prospective, multi-site, single (rater)-blind, RCT using a group comparison design between involving the intervention, MBCT, and a comparison condition, Depression Relapse Active Monitoring (DRAM) with follow-up over 2 years. Both interventions are provided in addition to TAU. All participants receive DRAM with half the sample randomised to additionally receive MBCT. Participants continue their usual treatment during the course of their participation in the trial. We avoid any attempts to standardise routine clinical care including medication beyond the recommendations of DRAM. The study is being conducted in compliance with the Helsinki Declaration and has been approved by the following governing ethics committees: Alfred Hospital Ethics Committee (280/07); Barwon Health Research and Ethics Advisory Committee (07/86); Monash University Standing Committee on Ethics in Research Involving Humans (CF07/1275-2007/019MCC; CF08/1031-2008000509); Peninsula Health Human Research & Ethics Committee (2007-53); Southern Health Human Research Ethics Committee (07056B); and The Melbourne Clinic Research Ethics Committee (189). Written informed consent is required for all participants.

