### The Interventions

#### MBCT

##### Description

MBCT is a manualised program delivered by an instructor in 8 weekly 2-hour group training sessions involving up to 10 clients; optional 3-monthly 'booster sessions' are also delivered. Sessions incorporate mindfulness practices including meditation and also CBT exercises [28]. Homework for participants includes formal daily meditation practices and exercises for the development of mindful awareness within everyday activity.

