### Power analysis

A power analysis was conducted using estimates of annual relapse rates obtained from the literature. Systematic reviews and meta analyses were mainly utilised including: no treatment (or placebo) only [35-38]; psychological treatment alone; effect in recurrent depression of medication alone [35,37,38]; and combined psychological and pharmacotherapy [39,40]. From these sources, anticipated relapse rates over a 2-year period were: no treatment, 56%; MBCT alone, 31%; medication alone, 31%; and MBCT and medication together, 15%. Based on findings from recruitment in our pilot study, we assumed that 70% of the sample would be taking at least some reasonably effective dose of medication, and 30% would not. Applying the subgroup specific odds ratios suggested the following relapse rates as likely over a 26-month period: MBCT group 21.5%; and DRAM group 41.7%. A power analysis showed that to detect this difference using an uncorrected chi-squared statistic at 80% power and α = 0.05 would require a sample size of 82 participants to complete the full 26 months in each of the MBCT and DRAM groups [41]. Further, assuming a dropout rate of 20% led to a recruitment target of 102 participants for each group.

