### Statistical analysis

#### Primary outcomes

Intention-to-treat (ITT) analysis will be the primary analytic framework. Groups will be compared using chi-square or Fisher's exact test for proportions and *t*-test or Mann-Whitney-test for continuous variables. Time to relapse/recurrence of depression will be examined using the Kaplan-Meier survival analysis. The Cox proportional hazards regression analysis will be used to examine the effect of covariates such as treatment expectations on time to relapse/recurrence. Per protocol (PP) analyses will also be undertaken. As in previous trials, at least four sessions will be considered as the minimal treatment dose. However, as the MBCT program is sequential and participants are strongly encouraged to attend all sessions, or at least miss no more than one [63], we will also examine outcomes for people who attended the recommended dose of therapy, being 7-8 sessions.

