#### Economic evaluation

The incremental cost of MBCT is the cost of treatment less any savings in health service use. Results of incremental cost-effectiveness analysis will be subject to extensive probabilistic sensitivity analysis [66] using @Risk software, which allows the results to be presented as cost-effectiveness acceptability curves [67]. The cost-utility of MBCT + DRAM compared to DRAM alone will be compared using repeated-measures ANOVAs.

As recommended by Hollis and Campbell [68], sensitivity analyses will be undertaken across these analyses to examine the potential influence of the missing data using various forms of imputation. Where appropriate, given the design of the study, multilevel modelling will be employed [69].

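### MBCT is given in therapy groups and DRAM individually, but neither the sample size nor the named primary tests allow for therapy group; if outcomes within groups are positively correlated, the unadjusted test is anti-conservative and a valid test has less than 80% power

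*Protocol article*

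**What the plan says.** The Description of MBCT gives the format as "8 weekly 2-hour group training sessions involving up to 10 clients", led by an instructor. Under Research design, "All participants receive DRAM with half the sample randomised to additionally receive MBCT". The section on DRAM has it taught by a research assistant at the intake interview, after which the participant self-monitors; no groups are formed. The Randomisation section assigns individuals, and Assessments (under Procedure) adds that they are randomised in cohorts, with both arms' follow-up timed to the MBCT programme run for their cohort.

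The Power analysis section takes relapse of 21.5% with MBCT and 41.7% with DRAM over 26 months and states that "to detect this difference using an uncorrected chi-squared statistic at 80% power and α = 0.05 would require a sample size of 82 participants" with complete follow-up in each arm. The only inflation is for 20% dropout.

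For the primary outcome, "Groups will be compared using chi-square or Fisher's exact test for proportions", with Kaplan-Meier for time to relapse and Cox regression for covariates, of which treatment expectations are the example. Under Economic evaluation, after a sentence on missing-data sensitivity analyses, the last line reads: "Where appropriate, given the design of the study, multilevel modelling will be employed".

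**The concern.** Members of one MBCT group share an instructor, fellow members and 16 hours of sessions (8 × 2 hours). Their relapse outcomes may therefore be more alike than those of unrelated participants, while no such link is created among those who receive DRAM alone. This is a partially nested design. The tests named for the primary outcome, and the calculation that sizes the trial for one of them, take every participant as independent.

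If the within-group correlation is positive, the variance of the MBCT relapse proportion is understated. The unadjusted confidence interval is then too narrow and the p-value too small, and an analysis that does respect the groups has less power than stated. The error runs in the direction of declaring benefit, in a trial whose Discussion looks to its findings to guide a funding decision. It also leaves two candidate primary p-values, one unadjusted and one multilevel, with no stated rule for choosing between them.

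**Working it through.** **Inputs from the article.** Relapse p₁ = 0.215 (MBCT) and p₂ = 0.417 (DRAM), so the difference is d = 0.202; α = 0.05; 80% power; 82 completers per arm; MBCT groups of up to 10. The article does not say whether α is one- or two-sided.

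**Assumptions.** The ICC is not given, so I use 0.01, 0.02, 0.05 and 0.10. For analysed members per group I use m = 8 (a group of 10 after the planned 20% dropout) and m = 10 (the stated maximum with no loss, hence an upper bound).

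**Step 1: reproduce 82.** The pooled proportion is p̄ = (0.215 + 0.417)/2 = 0.316, so p̄(1−p̄) = 0.2161. The arm variances are p₁(1−p₁) = 0.1688 and p₂(1−p₂) = 0.2431. Then

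n = [1.96·√(2 × 0.2161) + 0.8416·√(0.1688 + 0.2431)]² / 0.202² = (1.2886 + 0.5401)² / 0.0408 = 81.96, i.e. 82.

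Power at 82 per arm is 80.0%. Among variants, an unpooled variance gives 80, a continuity correction 92 and a one-sided test 65; an arcsine calculation gives 81.2, which also rounds up to 82. The stated figure is thus the ordinary independent-sample result, with no room in it for a design effect.

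**Step 2: cluster the MBCT arm only.** The design effect is D = 1 + (m − 1)·ICC for MBCT and 1 for DRAM.

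- Type I error of the unadjusted test: under the null the true variance exceeds the assumed one by (D + 1)/2, so the error is 2·{1 − Φ(1.96/√[(D + 1)/2])}.
- Power of a test that allows for groups: Φ{(d − 1.96·SE₀)/SE₁}, with SE₀ = √[p̄(1−p̄)(D + 1)/82] and SE₁ = √[(D·p₁(1−p₁) + p₂(1−p₂))/82]. At D = 1 this is the formula of Step 1.

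Worked case, m = 8 and ICC 0.05: D = 1 + 7 × 0.05 = 1.35. The variance ratio is 2.35/2 = 1.175, and 1.96/√1.175 = 1.808, giving a type I error of 7.1%. SE₀ = √(0.2161 × 2.35/82) = 0.0787 and SE₁ = √[(1.35 × 0.1688 + 0.2431)/82] = 0.0758. So (0.202 − 1.96 × 0.0787)/0.0758 = 0.63, and power is 73.6%.

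| ICC (assumed) | D, m = 8 | Type I error | Power | D, m = 10 | Type I error | Power |
|---|---|---|---|---|---|---|
| 0 | 1.00 | 5.0% | 80.0% | 1.00 | 5.0% | 80.0% |
| 0.01 | 1.07 | 5.4% | 78.7% | 1.09 | 5.5% | 78.3% |
| 0.02 | 1.14 | 5.8% | 77.4% | 1.18 | 6.1% | 76.7% |
| 0.05 | 1.35 | 7.1% | 73.6% | 1.45 | 7.7% | 71.8% |
| 0.10 | 1.70 | 9.2% | 67.6% | 1.90 | 10.4% | 64.4% |

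**Step 3: number of groups.** 102 recruits at 10 or 8 per group form 102/10 ≈ 10 to 102/8 ≈ 13 groups. The formulas above are large-sample approximations and include no penalty for so few clusters.

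**The case against.** The strongest reply is that the plan does provide for multilevel modelling. The sentence stands in a separate closing paragraph, after one that refers to sensitivity analyses across the analyses generally, so it can be read as covering the whole statistical section, and its reference to the study's design may well have nesting in mind. A reader might infer that the plan treats everyone as independent throughout; that sentence means the documents do not support so flat a statement. What remains is that it is conditional, could equally refer to sites or repeated measures, does not say that the primary test is replaced or adjusted, and cannot alter a sample size already calculated. Model detail may fairly be left to an analysis plan, but the sample size and the primary tests are fixed in this article.

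A second reply is that the harm depends on an ICC that nobody has stated. This stands. At 0.01 the effect is small, at zero there is none, and nothing in the article supports 0.10 in particular.

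Third, between-group differences may be modest: the programme is manualised, instructors take one common 44-hour course, and two sessions from each group are audited for fidelity. A reader might infer from the emphasis on brief training that the instructors are novices and the ICC must be large. Therapist training describes clinicians experienced in mental health who need no background in meditation, so that inference fails.

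Fourth, both arms share recruitment cohorts. Variation due to a cohort's timing or place affects both arms and partly cancels in the comparison. This is a fair point about how the model should be built; it does not remove correlation that arises inside the therapy group.

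**Conclusion.** The concern holds in conditional form. The sample size contains no allowance for therapy group, and the named primary tests have no term for it. The stated 80% power and the nominal 5% level are therefore right only if the ICC is zero. For an assumed ICC of 0.01 to 0.05 and 8 to 10 analysed members per group, type I error is about 5.4 to 7.7% and the power of a valid test about 79 to 72%. At 0.10 the figures are about 9 to 10% and 68 to 64%.

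These results rest on the assumed ICC and group size, equal groups, a normal approximation and the pooled two-sided formula that reproduces 82. A reader might go further and say that the primary p-values will be too small. The documents do not establish that, because they give no ICC; they establish only that the primary tests as named offer no protection if it is positive.

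**What to change.** - Move the multilevel provision into the primary outcomes section and attach it to both the relapse proportion and time to relapse. Name therapy group as the cluster in the MBCT arm only, with each DRAM participant as a singleton: a partially nested mixed model for the proportion, and shared frailty or cluster-robust standard errors for the Cox model.
- Specify a small-sample correction, given roughly 10 to 13 groups.
- Consider recruitment cohort, which both arms share, as a stratum or covariate. If each cohort forms a single MBCT group, the therapy-group term is then what remains in the MBCT arm after the shared cohort effect.
- State which analysis supplies the primary p-value, and settle this before outcomes are compared by arm.
- Restate the power at 82 per arm over an assumed ICC range, with the design effect in the MBCT arm. Do not enrol more.

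The cost is analysis wording and one recalculation. Therapy group should be recoverable, since sessions are audited by group and assessments are timed to each cohort's programme, but the article does not say that it is recorded for each participant, so this should be confirmed. The price is a slightly wider confidence interval and a lower stated power.

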### Participants

#### Recruitment

Participants are recruited from private and public community health services and through notices placed in local media in metropolitan Melbourne and the regional city of Geelong, located in the state of Victoria, Australia. Also targeted are public mental health services across multiple sites and ECT clinics where the more severely affected individuals are likely to be treated as, from a health economics perspective, this group is likely to have the greatest impact on costs.

#### Selection criteria

Inclusion criteria include meeting DSM-IV criteria for three previous episodes of MDD [DSM-IV diagnosis of either MDD (Recurrent) or Bipolar Disorder I or II], aged between 18-75 years, and able to speak and read English fluently. Current use of medication, including antidepressants and mood stabilisers, is allowed. Exclusion criteria include: current episode of MDD; current symptoms of a psychotic disorder, or a past diagnosis of a psychotic disorder where the treating clinician believes the therapy may be contraindicated; current significant eating disorder or obsessive-compulsive disorder; organic mental disorder or pervasive developmental delay; current borderline or antisocial personality disorder; current alcohol or drug dependency other than tobacco; current benzodiazepine intake of more than 20 mg diazepam equivalent; and inability to give informed consent.

#### Randomisation

Assignment of individual participants to MBCT + DRAM or DRAM alone is undertaken by the study statistician using a minimization routine balancing numbers in groups as randomisation proceeds [42]. The statistician works independently of staff involved in the recruitment, assessment and management of participants in the study. To guard against confounding by major differences in other treatment exposures, randomisation is stratified by: medication (currently taking antidepressants and/or mood stabilisers: yes/no); site of referral (primary care, secondary care, specialist clinic): diagnosis (bipolar disorder: yes/no); and gender.

#### Retention

Given the 2-year follow-up proposed for this study, and the requirement of monthly assessments, attention to retention strategies is crucial to the success of the trial as completeness of follow-up has a significant effect on the quality and validity of the analysis. Strategies we implement to limit attrition include: minimising response burden as far as possible such as having flexibility in how assessments can be completed; employing staff experienced in communicating with research participants; establishing a project name ("DARE - Depression Awareness Recovery Effectiveness") and identity (professionally designed project logo, website, wallet card with key contact numbers); provision of reimbursement that acknowledges the participants' time and effort; and greeting cards and quarterly newsletters to maintain positive contact between assessments.

### Measures

#### Diagnosis and eligibility

##### Composite International Diagnostic Interview 2.1 Auto Lifetime version (CIDI-LT)

Diagnostic inclusions and exclusions are assessed using the appropriate sections of the Composite International Diagnostic Interview 2.1 Auto Lifetime version (CIDI-LT). The CIDI 2.1 is a highly standardised instrument designed to be administered by lay interviewers. The CIDI 2.1 was used in preference to the more recent World Health Organisation CIDI (WHO CIDI) because the latter is not available in a 12-month form and the former had stronger evidence supporting its validity [43,44]. To minimise participant burden, in this design exclusion criteria related to psychosis, personality disorder, organic mental disorder or pervasive developmental delay are not formally assessed. Instead, reliance is placed on the treating clinician to screen out ineligible candidates.

#### Primary outcome: relapse/recurrence of MDD

##### Composite International Diagnostic Instrument 2.1 Auto 12 month version (CIDI-12)

Episodes of depression are assessed retrospectively during a face-to-face interview using the CIDI Auto 2.1 12 month affective disorders modules. Several questions from the WHO CIDI are added to give more precise details of episodes including number of episodes (where there was at least 2 weeks in remission between episodes), the month that the first/only depressive episode commenced, and total number of days depressed.

##### Patient Health Questionnaire

In the study the Patient Health Questionnaire-2 [PHQ-2 - [45]] and the PHQ-9 [46] are used to monitor for the presence and severity of depressive symptoms each month. The PHQ-2 is a screening tool for depression that comprises two questions addressing anhedonia and depressed mood with frequency ratings 0 (not at all) to 3 (nearly every day). The PHQ-9 comprises the nine criteria upon which the diagnosis of DSM-IV depressive disorders is based. Both instruments have been found to be reliable and valid [45,46]. As part of DRAM, participants are trained on how to complete the PHQ-2 and PHQ-9 then prompted monthly to self-monitor via their preferred medium of SMS, telephone or internet. To facilitate monitoring, the PHQ-2 is provided on a wallet card which also has their project ID and password for online completion. Participants reporting scores ≥3 are directed to complete the PHQ-9 and encouraged to seek appropriate assistance using automated feedback. The full PHQ-9 is administered every 3 months regardless of PHQ-2 score.

##### Time to first clinical intervention

We expect an active property of DRAM in prompting participants to seek help for depressive symptoms at an earlier stage than would occur without this self-monitoring intervention. Thus, although providing some control for treatment expectation and ethically optimising the design, this intervention may reduce the between-group differences with respect to depressive relapse so that time to first clinical intervention is an important adjunctive measure. The General-practice Users' Perceived-need Inventory (GUPI) short form [47] is a three-item measure of perceived need for mental health care that was slightly modified to assess whether there had been a clinical intervention in the past 3 months, and if so, when this was initiated. Study design also includes tracking of medication changes over the course of the project with onset of an antidepressant or increase in dose assumed to signal an incipient relapse.

#### Patient expectations

##### Credibility/Expectancy Questionnaire

The Credibility/Expectancy Questionnaire [CEQ - [48]]) is used to assess therapy credibility and client expectancy for improvement, as potential confounds for outcome. The CEQ has high internal consistency and good test-retest reliability and has been shown to discriminate between different treatment rationales [48]. The instructions for the CEQ are modified so as to be appropriate for participants in both groups.

##### Belief about relapse

Belief about relapse is assessed by asking participants to indicate how likely it was that they would experience depression again in the next year on a fully anchored scale from "very unlikely" (score 1) to "very likely" (score 5).

#### Secondary outcomes and process measures

A range of measures are included to examine the factors shown in Figure 1 in terms of both outcome and mediation. Measures include the State-Trait Anxiety Inventory ([STAI - [49]]), International Personality Item Pool Neuroticism and Openness to experience subscales [IPIP - [50,51]]), Five Facet Mindfulness Questionnaire [FFMQ - [52]]), the Ruminative Response Scale [RRS - [53]]), the Hill-Bone Medication Taking Scale [54] and locally-developed measures of mindfulness practice and medication adherence. Outcome in relation to work and social functioning is assessed using the Work and Social Adjustment Scale [WSAS - [55]]) and health-related quality of life using the Assessment of Quality of Life instrument [AQoL -[56]]).

#### Economic analysis

Service utilisation by self-report is assessed with instrumentation used in the most recent (2007) Australian National Survey of Mental Health and Wellbeing. This instrument was used in the first national survey in 1997, but has been updated to take into account identified deficiencies in the earlier instrument [57]. It includes some elements of the service utilisation section of the WHO CIDI [44]. It also contains questions relating to levels of perceived need for mental health care and so provides a consumer appraisal of the relative adequacy of overall service provision [58-60]. As the instrument was prepared drawing on a national expert group with support of the Australian Bureau of Statistics, this likely represents the best developed instrument for collection of service utilisation data in Australia.

In order to estimate costs associated with lost productivity, every 3 months participants in the study are asked to record the number of days they had been absent from their usual work or occupation due to illness or disability. Also collected is their account of how many of these days were due to depression or related problems with their mental health. Employment status and, for those working, current occupational status are rated using the *Australian and New Zealand Standard Classification of Occupations *[61]. The AQoL will also be used to assess the cost-utility of MBCT in terms of quality-adjusted life years (QALYs).

### Procedure

#### Assessments

Experience from pilot work [62] indicated that the primary reason for exclusion from that study was failure to meet the selection criteria related to MDD. Referrals to the project are therefore screened over the phone using a brief questionnaire based on key questions from the Depression module of the Lifetime version of the CIDI 2.1. Potentially eligible candidates then are invited to complete an intake assessment to assess eligibility and collect baseline data. Following the intake assessment, eligible participants are randomised in cohorts to treatment condition. For participants in both treatment conditions, PHQ assessments are completed at intake and then at monthly intervals from the fourth week of the MBCT program conducted for their cohort. The CIDI 2.1 12 month version, Service Utilization, Hill-Bone Medication Taking Scale, IPPI, CEQ and Beliefs about Relapse are completed at 12 months and 24 months following the conclusion of the MBCT program. The CEQ is also administered at the fourth and eighth week of the MBCT program and Beliefs about Relapse at 8 weeks. The remaining self-report assessments are administered 3 monthly.

